**Fig 2 pone.0332985.g002:**
[figure not shown]
Sample collection, pretreatment, and multi-omics analysis pipeline. A total of six multi-omics assays will be conducted, with sample utilization stratified by type and collection time point. Bronchoalveolar lavage fluid (BALF) samples collected within 24 hours of enrollment will first utilize the original fluid for clinical mNGS for pathogen diagnosis, alongside metagenomic microecology analysis and virus spectrum analysis. All samples will undergo centrifugation within 24 hours of collection. Following centrifugation, the BALF supernatant will be subjected to proteomic and metabolomic assays, while the resulting cell pellet will be utilized for transcriptomic and single-cell transcriptomic analyses. Concurrently collected blood samples will also be centrifuged, with the plasma used for proteomic and metabolomic assays, and peripheral blood mononuclear cells (PBMCs) utilized for bulk transcriptomic and single-cell transcriptomic analyses. For the late phase, BALF and blood samples collected prior to extubation (with priority given to day 10 ± 2) will focus on transcriptomic and single-cell transcriptomic analyses: centrifugation-derived BALF cell pellets and blood PBMCs will be exclusively used for these assays.

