### Sample collection, and multi-omics profiling

For enrolled patients, peripheral blood and BALF samples will be collected at two time points: within 24h after enrollment and before tracheal extubation. For patients who cannot be extubated within 7–14 days, samples will be collected during this 7–14 day window, with priority given to day 10 ± 2 (Fig 2).

For blood sampling, patients must be in a fasting state prior to blood collection. A total of 10–15 mL of blood will be collected using anticoagulant tubes, which will then undergo pretreatment before separate storage or detection. Within four hours of sampling, centrifugation will be conducted at 3000 r/min for 10 minutes. The resulting plasma will be aliquoted into 1.5 mL EP tubes at 500 μL per tube for subsequent proteomics and metabolites detection. For the remaining sample, equal volumes of phosphate buffered saline (PBS) and Ficoll lymphocyte separation solution will be added, followed by centrifugation at 1000g for 20 minutes to collect PBMCs. After adding 5 mL of PBS, the mixture will be centrifuged at 400g for 5 minutes, the supernatant will be discarded, and PBMCs will be resuspended in cell cryopreservation solution before aliquoting into EP tubes at 1 mL per tube. The PBMC samples will be used for RNA-seq and scRNA-seq. The samples will be stored at −80°C before multi-omics detection.

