For BALF sampling, two tubes of BALF samples will be collected. One tube, containing no less than 10 mL, will undergo pretreatment for subsequent RNA-seq, scRNA-seq, proteomics and metabolites detection. The other tube, with a volume of at least 5 mL, will be directly submitted for clinical mNGS pathogen testing, as well as for metagenomic microbial spectrum analysis and meta-transcriptomic expression profiling. For reserved samples, 6 mL of BALF will be centrifuged at 4000g for 10 minutes. The supernatant will then be aliquoted into 1.5 mL EP tubes at 400 μL per tube, while 1 mL of Trizol will be added to the remaining cell pellet, followed by vortex mixing. All aforementioned samples, along with the remaining BALF, will be labeled and stored at −80°C. The supernatant will be used for proteomics and metabolites detection, while the bottom cell-sedimentation will be used for bulk RNA-seq and scRNA-seq. Since BALF sampling is invasive, the patient’s condition will be evaluated prior to sampling. If the attending physician determines that further sampling is inappropriate or the patient declines sampling, the procedure will not be performed. During sampling, certain adverse events will be documented. Subsequently, the attending physician will assess the feasibility of subsequent sampling. If the risk of further BALF sampling is deemed relatively high, the patient will be excluded from the study.

BALF samples collected for mNGS-based infectious disease diagnosis will be transported immediately to the corresponding testing center for mNGS pathogen detection. Any samples that could not be shipped on the day of collection should be temporarily stored at 2–8°C. Other collected samples will underwent appropriate preprocessing before being preserved at −80°C. Following the enrollment of all patients, all samples will be uniformly transported to the PLA General Hospital via cold chain logistics for multi-omics analysis. Crucially, all samples will be subjected to no more than one freeze-thaw cycle prior to testing to maintain sample integrity. The detailed methods for multi-omics detections are summarized in S5 File.

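### As written, the only BALF cell pellet described goes into Trizol and is then assigned to single-cell RNA-seq; the handling text and the planned BALF single-cell outcome must be reconciled

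*Protocol article*

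**What the plan says.** All of the following is in the protocol article, under Sample collection, and multi-omics profiling, unless another place is named.

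- **Reserved tube:** "One tube, containing no less than 10 mL, will undergo pretreatment for subsequent RNA-seq, scRNA-seq, proteomics and metabolites detection".
- **Spin:** "6 mL of BALF will be centrifuged at 4000g for 10 minutes". The supernatant is aliquoted for proteomics and metabolomics.
- **Pellet:** "1 mL of Trizol will be added to the remaining cell pellet, followed by vortex mixing".
- **Storage:** "All aforementioned samples, along with the remaining BALF, will be labeled and stored", at −80°C.
- **Use of the pellet:** "the bottom cell-sedimentation will be used for bulk RNA-seq and scRNA-seq". The Fig 2 legend agrees for the first time point: "the resulting cell pellet will be utilized for transcriptomic and single-cell transcriptomic analyses". For the late time point it reserves the BALF pellets for the same two assays.
- **Timing:** "Following the enrollment of all patients, all samples will be uniformly transported" to the lead hospital for omics testing.
- **Blood, for the same two assays:** "PBMCs will be resuspended in cell cryopreservation solution before aliquoting into EP tubes". Trizol is not mentioned.

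The Outcomes section lists scRNA-seq of both blood and BALF, early and before extubation, among the additional outcomes. The Purpose of the study section aims to identify the immune cell subtypes that determine onset and prognosis, and gives alveolar macrophages as its first example.

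**The concern.** Bulk and single-cell RNA-seq need different starting material. Bulk sequencing can use pooled RNA from dissolved cells. Single-cell sequencing needs cells that are still separate, because each transcript must be traced to its cell. Trizol dissolves cells and mixes their RNA, and this cannot be undone. The text sends one pellet through Trizol and then assigns it to both assays.

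At stake is the lung-side part of the cell-subtype aim. Alveolar macrophages are lung cells, and blood mononuclear cells cannot stand in for them. The Discussion also presents single-cell resolution as the anchor of the multi-omics work and names alveolar epithelial and stromal cells. BALF sampling is invasive, so material lost to lysis is not easily replaced.

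**Working it through.** No statistical figure is in dispute. The check follows the BALF material and asks whether any of it reaches scRNA-seq as intact cells.

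1. **Spun portion.** 6 mL gives supernatant and one pellet. The text describes no division of the pellet before Trizol is added, so the whole pellet becomes lysate.
2. **Unspun portion.** At least 10 mL is reserved and 6 mL is spun: 10 − 6 = at least 4 mL left. This remainder is frozen at −80°C, no cryoprotectant is mentioned, and it is not assigned to scRNA-seq. The text assigns scRNA-seq to the sediment.
3. **Second tube.** This tube (at least 5 mL) goes to clinical mNGS, metagenomic and meta-transcriptomic work, not to host single-cell work.
4. **Fresh processing.** None is described for BALF cells. Samples for omics are held frozen and shipped only after enrollment closes.
5. **Comparison with blood.** Mononuclear cells meant for the same two assays are kept in cryopreservation solution. The section thus preserves cells for single-cell work in one compartment and lyses them in the other.

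None of the four BALF routes supplies intact cells to scRNA-seq as written.

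**Extent.** With the enrollment target of 200 patients and two time points, the ceiling is 200 × 2 = 400 pellets. With 165 patients it is 165 × 2 = 330. Both are loose upper limits:

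- BALF sampling may be omitted on the physician's judgement or the patient's refusal, and patients judged at high risk from further sampling are excluded.
- At the assumed 28-day mortality of about 40%, 200 × 0.40 = 80 deaths would be expected, some possibly before the second sample. The article gives no timing from which to count them.
- The article does not say that scRNA-seq will be run on every sample.

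**What does not depend on this.** The primary outcome is 28-day survival or death. The sample size rests on 66 deaths and 40% mortality (66 / 0.40 = 165). Neither uses BALF single-cell data.

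**The case against.** The strongest reply is that this is a condensed article. Assay methods are in the S5 File, and a researcher's manual and site training cover sample collection and preservation. The Fig 2 legend sends the pellet to both assays without mentioning Trizol. The reserved tube also holds more than is spun. One sentence may therefore have merged two workflows, with intact cells kept somewhere in practice.

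That possibility stands, and it limits the claim. A reader might infer that BALF single-cell data cannot be produced at all. The article does not support this: it shows only that the procedure as printed names no usable source. The reply does not remove the conflict, however. S5 is cited for detection methods, while collection and pretreatment are printed in the article down to volumes and spin speed. If S5 or the manual does describe a separate cell portion, it disagrees with the printed text and the two still need reconciling.

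A reader might also infer that the cell-subtype aim would rest on blood alone. That goes too far. BALF bulk RNA-seq, proteomics, metabolomics and BALF cell counts with classification still inform the lung side.

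Finally, it is fair to say that BALF scRNA-seq is an additional outcome, and that the modelling section does not separately name single-cell data as a model input.

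**Conclusion.** The point holds as an internal contradiction: the stated BALF handling is incompatible with the planned BALF scRNA-seq. The consequence is loss of single-cell resolution in the lung compartment, at up to two time points per sampled patient. The 400 pellets are a ceiling, not an estimate of samples lost, and the pellets remain suitable for bulk RNA-seq. PBMC scRNA-seq, BALF proteomics, metabolomics and cell counts, the primary outcome and the sample size are unaffected.

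The conclusion rests on two things: that Trizol lyses cells, which is general laboratory knowledge and not a statement in the article, and that sites follow the printed procedure. It needs correcting because a listed outcome and part of the stated purpose depend on it, not because the main inference on 28-day mortality is at risk.

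**What to change.** **Handling.** Reconcile the sample section, the Fig 2 legend and the Outcomes section. Limit Trizol to the BALF portion used for bulk RNA-seq. State which separate portion is kept as intact cells in cell cryopreservation solution, as is done for PBMCs. The uncentrifuged remainder of at least 4 mL is one candidate, subject to cell yield. The article gives no yield, so it cannot be assumed that this volume is enough.

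**Samples already in Trizol.** State that only bulk RNA-seq is possible for them. Report how many patients have usable BALF single-cell material at each time point, and restrict conclusions about BALF cell subtypes to those patients. If a separate cell portion has been kept in practice, say so and correct the printed text.

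**Cost.** This takes a revised procedure and site manual, a training update at ten centers, and one extra tube per sampling. Recruitment began in November 2023 and was due to end in November 2025, so a change in handling may reach few samples, and lysed samples cannot be recovered. The reporting part of the fix can be applied whatever the recruitment status.

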### Participant recruitment

Participants will be recruited from ten medical centers in tertiary general hospitals in North China, including the First Medical Center of Chinese PLA General Hospital, the Sixth Medical Center of Chinese PLA General Hospital, the Eighth Medical Center of Chinese PLA General Hospital, Beijing Shijitan Hospital, Beijing Anzhen Hospital, AMHT Group Aerospace 731 Hospital, Zhengzhou Central Hospital, Henan Provincial People’s Hospital, the First Affiliated Hospital of Zhengzhou University and First Hospital of Shanxi Medical University.

Patients with ARDS will be invited to participate in this study upon admitting the branch center. Those who meet the inclusion criteria and provide signed informed consent will enter the screening period (S1 File). During the screening visit, trained researchers (physicians) will confirm the eligibility based on symptoms, laboratory results, and chest X-ray or CT image, and review every inclusion and exclusion criterias. Patients who meet the exclusion criteria will be excluded from this study within 24 hours. The recruitment period is set for 24 months, spanning from November 2023 to November 2025.

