### Follow‑up schedules

At the 28-day mark, patients will be assessed for the primary outcome of survival or death. At this point, the attending physician will report the primary outcome, and the data collection database will then document the 28-day mortality rate, as well as the duration of ICU and hospital stays, along with other relevant outcomes. During the study period, specific measurements will be taken at predetermined time points: day 1, day 3 ± 1, day 7 ± 1, day 14 ± 2, day 21 ± 2, day 28 ± 2, and before extubation (with priority to day 10 ± 2), discharge or death. The following parameters will be recorded: inflammatory markers, arterial blood gas, coagulation, blood glucose, blood lipids, electrolytes, myocardial enzymes, immune indexes, cell count and classification of BALF and etiological examination. 28-day administration of antibiotics, neuromuscular blockers, vasoactive agent, hormones and immunosuppressants will be tracked. The measurement and collection schedule of this experiment are summarized in the follow-up form (Table 1).

**Table 1 pone.0332985.t001:** The schedule of measurements and visits of this trial.

Timeline (day)	Screening	Follow-up								
	d1	d3 ± 1	d7 ± 1	before extubation (priority: d10 ± 2)	d14 ± 2	d21 ± 2	d28 ± 2	discharged/death (≤28 days)	d1-28	d28
**Informed consent form**	Χ									
**Inclusion/exclusion criteria**	Χ									
**Demographic data**	Χ									
**History of diseases**	Χ									
**ARDS risk factors**	Χ									
**Clinical symptom**	Χ	Χ	Χ	Χ	Χ	Χ	Χ	Χ		
**Imaging**	Χ	Χ	Χ	Χ	Χ	Χ	Χ	Χ		
**APACHE Ⅱ scores**	Χ	Χ	Χ	Χ	Χ	Χ	Χ	Χ		
**SOFA scores**	Χ	Χ	Χ	Χ	Χ	Χ	Χ	Χ		
**mechanical ventilation parameter**	Χ	Χ	Χ	Χ						
**respiratory mechanics**	Χ			Χ						
**pulmonary ultrasound score**	Χ			Χ						
**cardiac echocardiography**	Χ			Χ						
**pulse indicator continuous cardiac output parameters**	Χ			Χ						
**mNGS detection**	Χ									
**Clinical pathogen detection**	Χ	Χ	Χ	Χ	Χ	Χ	Χ	Χ		
**Laboratory examination**	Χ	Χ	Χ	Χ	Χ	Χ	Χ	Χ		
**BALF cell count and classified examination**	Χ			Χ						
**Samples**	Χ			Χ						
**Antibiotic use record**									Χ	
**vasoactive agent use record**									Χ	
**neuromuscular blockers, sedative and analgesic drugs use record**									Χ	
**Adverse events**									Χ	
**28-day survival follow-up**										Χ
**28-day ICU length of stay**										Χ
**28-day ventilator-free days**										Χ

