
### Outcomes

The primary outcome of this study is the 28-day clinical outcome, which includes survival and death. The secondary outcomes include 28-day ICU length of stay and ventilator-free days. For patients with moderate to severe ARDS undergoing invasive mechanical ventilation, additional outcomes include RNA-seq, and scRNA-seq analyses of peripheral blood and BALF will be collected on 24h of inclusion and before extubation. For patients unable to be extubated within 7–14 days, samples will be collected during this period. Respiratory mechanics parameters, severe ultrasound indexes, EIT data, the correlation of physiological parameters will also be evaluated using binary analysis.

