### Sample size calculation

The study hypothesizes that the developed model will achieve an area under the ROC curve of at least 0.85 for predicting the 28-day mortality in ARDS patients, and the goal is to test if this value is greater than 0.70, which is considered the threshold for good discriminant ability. The study is designed with α = 0.05 and β = 0.10, and the proportion of lost follow-up or withdrawal is less than 10%. The sample size was calculated using PASS-16 software, which determined that at least 66 deaths must be observed for the study. Referring to previous literature, the 28-day mortality rate of ARDS patients is about 40% [4,7,8], and it is estimated that 165 patients with ARDS need to be enrolled in the study. In addition, given the stringent quality requirements of multi-omics testing for samples and to account for potential test failure rates, we aim to enroll 200 patients to ensure the final testing meets the predetermined sample size requirements.

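### Enrolled patients judged too risky for further BALF sampling leave the study altogether, which may select the 28-day mortality cohort on prognosis

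*Protocol article*

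**What the plan says.** Under Sample collection, and multi-omics profiling, the article schedules sampling after entry: "For enrolled patients, peripheral blood and BALF samples will be collected at two time points: within 24h after enrollment and before tracheal extubation". The second sample has its own window in patients who stay ventilated: "For patients who cannot be extubated within 7–14 days, samples will be collected during this 7–14 day window".

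The BALF paragraph of that section then gives two rules. Before a procedure the patient's condition is evaluated, and: "If the attending physician determines that further sampling is inappropriate or the patient declines sampling, the procedure will not be performed". After a procedure, adverse events having been documented, the physician considers whether later sampling is feasible, and: "If the risk of further BALF sampling is deemed relatively high, the patient will be excluded from the study".

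The second rule does not appear in the exclusion list under Inclusion and exclusion criteria. Participant recruitment describes exclusion as a screening step: "Patients who meet the exclusion criteria will be excluded from this study within 24 hours".

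Under Outcomes: "The primary outcome of this study is the 28-day clinical outcome, which includes survival and death". Follow‑up schedules adds: "At the 28-day mark, patients will be assessed for the primary outcome of survival or death". The sample size section hypothesises that "the developed model will achieve an area under the ROC curve of at least 0.85" for 28-day mortality, tested against 0.70. It requires 66 deaths, assumes about 40% mortality, derives 165 patients, and sets an enrolment target of 200 to cover assay failures.

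**The concern.** A prognostic cohort should be defined at entry and then followed to the outcome. Here membership can end after entry, on a clinician's view of how risky another bronchoscopic sample would be. In ventilated patients with moderate or severe ARDS that view is likely to depend on how the patient is doing, and so on the chance of dying by day 28. Removal that depends on prognosis can bias observed mortality and the marker–death associations. It can also leave a model that does not apply to patients like those removed. A larger enrolment does not repair this.

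Two features add to the problem. No threshold is given for the risk judgement, so the ten centres may apply it differently. Under Multi-Omics data analysis and integration, eight centres are to supply training data and two validation data, so such differences could shift case mix between the two sets.

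The rule also discards information for no analytic gain. According to the Fig 2 legend, the late sample serves only bulk and single-cell transcriptomics, while the day-1 samples feed all six assays. Excluding a patient over a later BALF can therefore remove a complete day-1 set together with the outcome.

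**Working it through.** **1. The plan's own figures.** Inputs from Sample size calculation: AUC 0.85 against 0.70, α = 0.05 (sidedness not stated), β = 0.10, loss or withdrawal below 10%, mortality 40%.

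With the binormal variance V evaluated under each hypothesis, a two-sided test and equal numbers of deaths and survivors:

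- deaths = [(1.96·√V(0.70) + 1.282·√V(0.85)) / 0.15]² = 58.8, rounded up to 59
- 59 / 0.90 = 65.6, rounded up to 66
- 66 / 0.40 = 165

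So 66 deaths and 165 patients reproduce. Those figures are not in dispute.

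**2. What removal does to the cohort.** The enrolment target is N = 200, so expected deaths are 200 × 0.40 = 80. Let f be the share removed under the BALF rule and m the 28-day mortality those patients would have had. The documents give neither, so both are assumptions.

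- deaths left = 80 − 200·f·m
- patients left = 200·(1 − f)
- fall in observed mortality = f·(m − 0.40)/(1 − f)

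| f | m | Deaths left | Patients left | Observed mortality |
|---|---|---|---|---|
| 5% | 60% | 80 − 6 = 74 | 190 | 38.9% |
| 5% | 80% | 80 − 8 = 72 | 190 | 37.9% |
| 10% | 40% | 80 − 8 = 72 | 180 | 40.0% |
| 10% | 60% | 80 − 12 = 68 | 180 | 37.8% |
| 10% | 70% | 80 − 14 = 66 | 180 | 36.7% |
| 10% | 80% | 80 − 16 = 64 | 180 | 35.6% |
| 15% | 60% | 80 − 18 = 62 | 170 | 36.5% |
| 20% | 60% | 80 − 24 = 56 | 160 | 35.0% |
| 20% | 80% | 80 − 32 = 48 | 160 | 30.0% |

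The third formula shows that the shift depends on m differing from 40%. At m = 40% it is zero for any f.

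**3. Power.** Using the same variance formula, two-sided, with the actual survivor-to-death ratio and every retained death entering the AUC test as the plan's calculation supposes:

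- 72 deaths of 190: 0.979
- 64 of 180: 0.967
- 56 of 160: 0.944
- 48 of 160: 0.919

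If only 165 were enrolled, 20% removed at 80% mortality leaves 66 − 26.4 = 39.6 deaths of 132, with power 0.856. Power holds up because at 1.5 survivors per death the test needs about 51 deaths before any dropout allowance, not 66.

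**4. The two sentences side by side.** The first acts before a procedure, also covers refusal, and its only consequence is that the sample is not taken. The second acts after a procedure, looks ahead to later ones, and ends participation. A physician who thinks a later BALF unsuitable could apply either. One keeps the patient in the cohort and the other does not.

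**The case against.** Several stronger readings are tempting, and the objections to them stand.

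- **The rule removes the sickest patients.** The text does not say so. The trigger is procedural risk, and severe haemodynamic instability is already an exclusion at entry. That the rule may selectively remove sicker patients is an inference, though a reasonable one, because the article ties the sampling decision to the patient's condition and to adverse events during sampling.
- **The study loses the deaths it needs.** Starting from 165 would suggest this, but the target is 200. With 10% removed at 70% mortality, exactly 66 deaths remain. Some scenarios fall below 66 (64, 62, 56 and 48 in the table), yet power stays above 0.9 in the scenarios run from 200. The 35 extra patients are meant for assay failure and the 10% allowance for loss, so neither is spare. Both address numbers only and cannot correct removal that depends on prognosis.
- **The two sentences flatly contradict each other.** Read in order, they sit at different decision points. They overlap and need reconciling, which is a weaker statement.
- **The table measures the bias.** It shows crude mortality and death counts under assumed inputs. The hypothesis concerns AUC, and neither the size nor the direction of any effect on AUC can be derived from the documents.

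It may also be said that the authors meant exclusion from further sampling only. The sentence says the study, and nothing elsewhere in the article softens it.

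**Conclusion.** The point holds as a risk of selection bias created by an explicit rule. Enrolled patients can be removed after baseline on an undefined judgement that plausibly relates to the primary outcome, and the article does not retain their day-28 status.

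Under assumed removal of 5–20% of 200 patients at 60–80% mortality, observed mortality would be 38.9% to 30.0% instead of 40%, and deaths 74 to 48 instead of 80. These ranges rest on f and m, which the documents do not give. If those removed died at the cohort rate, mortality would be unaffected. Lost power is not the argument, and neither a proven loss of the sickest patients nor an outright contradiction is supported. The sentence still needs correcting, because it decides who is counted for the primary outcome and the remedy is simple.

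**What to change.** Reconcile the two sentences so that stopping BALF sampling and leaving the cohort are separate events. A statement along these lines would do: a patient not sampled further remains in the study; day-1 data and samples already obtained, other permitted data and the 28-day outcome are kept; the reason for omitting BALF is recorded. The analysis then treats absent BALF as missing data and reports the number, reasons and 28-day outcomes of these patients, preferably by centre. Whether to sample a given patient remains the physician's decision and is not touched by this change.

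The cost is a short amendment and a CRF instruction. There is a real analytic downside: more patients will have incomplete BALF omics. This affects the early-fusion model and the selection of markers shared across omics, as well as the separate per-omics models. Timing also matters. Recruitment runs from November 2023 to November 2025, so outcomes of patients already excluded under the rule may have to be retrieved, where consent allows.
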